**Figure 1 biomedicines-11-02150-f001:**
[figure not shown]
Study design (BL ECT, bilateral electroconvulsive therapy; MST, magnetic seizure therapy; HAMD17, Hamilton Depression Rating Scale, 17 items [17]).

Initially, patients will receive a total of 12 sessions, including the first successful titration session. If the first titration session fails to induce adequate seizures, it will not be considered as part of the total number of sessions. After the 12th session, a clinical assessment will be performed. If the patient meets the criteria for remission, defined as a score of 7 or less on the 17-item Hamilton Depression Scale (HAMD17) [17], the sessions will be discontinued, and the patient will undergo a neuropsychological evaluation. If the patient does not achieve remission, they will receive an additional 6 sessions, bringing the total to 18, and will be re-evaluated and undergo a neuropsychological assessment. In this case, regardless of the response or remission, treatment will be discontinued after the 18th session. This is because evidence suggests that the number of sessions required to achieve response and/or remission typically ranges from approximately 6 to 15 sessions [18].

Following the final session, participants will undergo a comprehensive evaluation, including medical assessment, neuropsychological evaluation, laboratory tests, and cranial MRI. Finally, patients will be followed up for 6 months after completing the intervention, with re-evaluations at 3 and 6 months.

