### 2.8. Seric Biomarkers

Venous blood collections will be performed in the morning, fulfilling a minimum fasting period of 8 h comprising the following events:C1 (Collection 1): Performed on the day corresponding to the first session, prior to the procedure, taking advantage of the need for venipuncture. This will be considered the baseline sample;C2 (Collection 2): performed prior to 6th session;C3 (Collection 3): performed prior to 12th session;C4 (Collection 4): performed prior to 18th session (if any);C5 (Collection 5): performed 12 weeks after the start of the treatment;C6 (Collection 6): performed 24 weeks after starting treatment, coinciding with the 3-month medical evaluation.

Two 4 mL tubes of venous blood samples with anticoagulant (EDTA) will be collected before each event to prevent biochemical alterations related to the convulsive crisis. The collections will be performed at the ECT Service and immediately transported to the Neuroscience Laboratory LIM-27 for proper storage until the biochemical analysis is conducted. Post-treatment collections (C5, C6, and C7) will be scheduled with the staff and patient at the Neuroscience Laboratory LIM-27 after an 8 h fast. Brain-derived neurotrophic factor (BDNF) will be evaluated in the plasma using an immunofluorescence ELISA technique, which is highly specific for this type of evaluation. This technique has been shown to be more appropriate for state-dependent assessment of BDNF levels than other methods [61].

Our primary objective is to explore potential associations between changes in plasma BDNF levels and variations in depressive symptom scores and treatment response, as well as other clinical and neuroimaging outcomes (such as the variation in volume of each ROI). Additionally, we intend to compare the differences in plasma BDNF variation over time in patients undergoing ECT or MST. Moreover, we will evaluate the discrepancies in BDNF levels between patients who respond positively to treatment and those who do not, in each treatment arm.

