Based on previous studies [62,63,64,65], our hypothesis is that there will be a progressive increase in plasma BDNF levels, especially in the subgroup of patients with lower BDNF levels at baseline. We also hypothesize that there will be a positive correlation between improvement in depressive symptoms and an increase in BDNF, but its significance will be observed specifically in relation to plasma BDNF collected at time points C5 and C6. Additionally, we believe that higher baseline plasma BDNF levels may be associated with higher rates of treatment response and remission and, possibly, better cognitive outcomes. Furthermore, there will be a similar increase in plasma BDNF levels in patients who undergo ECT when compared to those who receive MST.

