We will define adverse events as events with intensity greater than “mild” and at least “remotely” associated with the intervention, as carried out in our previous studies [31]. The presence of adverse events and (hypo)manic upset will be compared between groups E and C using the chi-square test. This test will also be used to assess whether allocation group guessing occurred beyond chance.

Regarding the BDNF data, each collection during the follow-up will be individually analyzed in relation to the baseline values using Student’s *t*-test. The same analysis will be conducted to assess the differences between the treatment groups (ECT x MST) at each endpoint. Additionally, analysis of variance (ANOVA) will be used to evaluate potential differences in the means of plasma BDNF at different collection time points. A significance level of 5% will be adopted for all tests.

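### BDNF is tested by separate t-tests and an ANOVA with no stated patient effect, C4 exists only for session-12 non-remitters, and C5 and C6 do not fall on the depression visits

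*Protocol article*

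**What the plan says.** **Analysis (Protocol article, Section 2.9).** Against baseline, "each collection during the follow-up will be individually analyzed in relation to the baseline values using Student’s *t*-test". Between arms, "The same analysis will be conducted to assess the differences between the treatment groups (ECT x MST) at each endpoint". Across time, "analysis of variance (ANOVA) will be used to evaluate potential differences in the means of plasma BDNF at different collection time points". Neither pairing nor a patient term is mentioned. Earlier in the section, the linear hierarchical model set out for the autobiographical memory score is extended to all continuous secondary outcomes. One reason given for that model is that it uses the observed data without filling in missing values.

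**Sampling (Section 2.8).** C1 is taken before the first session, and C2 and C3 before sessions 6 and 12. C4 is taken before session 18, if there is one. C5 is "performed 12 weeks after the start of the treatment". C6 is "performed 24 weeks after starting treatment, coinciding with the 3-month medical evaluation". The next paragraph counts a C7 among the post-treatment collections, but the list stops at C6.

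**Hypothesis (Section 2.8).** A positive correlation between symptom improvement and BDNF rise is expected, and "its significance will be observed specifically in relation to plasma BDNF collected at time points C5 and C6".

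**Visits (Sections 2.1 and 2.5, Table 1).** Sessions are given twice a week. Remitters stop after session 12; the others go on to session 18. Then "patients will be followed up for 6 months after completing the intervention, with re-evaluations at 3 and 6 months". HAMD17 is scheduled at baseline, after session 6, and one week, three months and six months after the last session. A clinical assessment after session 12 decides remission.

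**The concern.** Three things do not fit together.

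- **Repeated samples.** Each patient gives several samples, but the tests as worded treat collections one at a time or as groups of means. A model that handles repeated and incomplete measurements is already in the same section.
- **Conditional collection.** Having a C4 sample depends on not having remitted by session 12. Remission is an outcome that the two treatments may affect differently, so the patients compared at C4 are no longer the randomised groups.
- **Two clocks.** C5 and C6 are counted from the start of treatment, while the HAMD17 follow-up visits are counted from the last session. The correlation hypothesis is tied to exactly these two collections.

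At stake are the power of the time comparison, the meaning of the C4 comparison, and knowing which HAMD17 score each late BDNF value is paired with. Draw dates cannot be corrected once the samples are taken.

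**Working it through.** **1. Does week 24 fall on the 3-month visit?** At two sessions a week, last session = sessions / 2 weeks. Post-acute visit = last + 1. Three-month visit = last + 13. Six-month visit = last + 26.

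| | 12 sessions | 18 sessions |
|---|---|---|
| Last session | week 6 | week 9 |
| Post-acute HAMD17 | week 7 | week 10 |
| 3-month HAMD17 | week 19 | week 22 |
| 6-month HAMD17 | week 32 | week 35 |
| C5 (week 12) after post-acute | 5 weeks | 2 weeks |
| C5 before 3-month | 7 weeks | 10 weeks |
| C6 (week 24) after 3-month | 5 weeks | 2 weeks |

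The stated coincidence is not reproduced. Placing the first session at week 0 gives weeks 18.5 and 21.5 for the 3-month visit. The most favourable reading adds a failed titration session (0.5 week) and counts three months from the post-acute visit (1 week more). It gives 9 + 0.5 + 1 + 13 = 23.5 for 18 sessions, but 6 + 0.5 + 1 + 13 = 20.5 for 12. No single reading gives week 24 for both groups. The gaps also differ by session-12 remission status, which is related to the outcome being correlated.

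C1 to C3 do line up approximately: C1 with baseline, and C2 and C3 just before the sessions after which depression is assessed.

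**2. Who has a C4?** Only patients who go on to session 18, hence only session-12 non-remitters. Of 88 patients, at an illustrative 35% remission, 88 × 0.65 ≈ 57 would have a C4. At 50% and 20% remission the counts are 44 and about 70. Section 2.9 mentions 35% when justifying a margin; it is not a forecast for session 12.

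**3. What does the form of the ANOVA change?** The inputs are 88 patients (Section 2.10) and five collections (C1 to C6 without C4). Three further inputs are assumptions, because the article gives none: equal correlation between collections of 0.3, 0.5 or 0.7, a linear rise from 0 to 0.3 SD, and complete data. Each setting was simulated 3,000 times at the 5% level.

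| Within-patient correlation | 0.3 | 0.5 | 0.7 |
|---|---|---|---|
| One-way ANOVA, type I error | 1.0% | 0.1% | 0.0% |
| One-way ANOVA, power | 29% | 20% | 12% |
| Patient effect included, type I error | 5.4% | 5.5% | 5.3% |
| Patient effect included, power | 54% | 71% | 91% |
| Last versus first collection, unpaired t, power | 50% | 51% | 51% |
| Last versus first collection, paired t, power | 65% | 80% | 94% |

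A check by formula: the squared deviations of the means (0, 0.075, 0.15, 0.225, 0.3) sum to 0.05625, so the noncentrality with a patient effect is 88 × 0.05625 / (1 − ρ) = 4.95 / (1 − ρ), that is 7.1, 9.9 and 16.5. The noncentral F distribution with 4 and 348 degrees of freedom then gives power of 54%, 70% and 92%, in line with the simulation.

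**4. What if it is a repeated-measures ANOVA?** The loss in step 3 disappears. But a complete-case version that includes C4 needs a C4 value from everyone, so it keeps only non-remitters at session 12.

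**The case against.** The article says only ANOVA and Student's t-test. Both are compatible with a repeated-measures ANOVA and a paired t-test, and a condensed article may leave that to the SAP. **This stands:** a reader might infer that the plan ignores repeated sampling, but the text does not say so. The power figures apply only on the one-way reading and rest on assumed values. Even then the error is in the conservative direction, not towards false positives.

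Section 2.9's BDNF paragraph may be a deliberate exception to the general rule. The Abstract calls neurophysiological biomarkers secondary outcomes, but the Discussion lists the secondary outcomes and the biomarkers separately. **This stands in part:** BDNF is not clearly under the rule. No reason is given for leaving it out, and neither reading of an ANOVA that covers C4 does better than the model already in the plan.

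Correlating improvement at the end of treatment with BDNF drawn later is a legitimate lagged hypothesis, so same-day pairing is not required. **This stands.** It does not remove the false statement that C6 coincides with the 3-month visit, and the article does not say that a lag is intended.

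C4 is openly conditional, and a paired comparison of C4 with baseline is valid as a description of patients treated that long. **This stands.** The comparison of arms at C4 remains selected.

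**Conclusion.** The point holds in a limited form. Three parts follow from the text alone:

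- C6 at week 24 contradicts a 3-month visit at about week 19 or 22.
- C5 at week 12 has no HAMD17 visit, and C7 is never defined.
- A C4 sample exists only for session-12 non-remitters, so an arm test there is not a randomised comparison. This takes each endpoint in Section 2.9 to mean each collection.

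The fourth part is conditional. The planned tests are either conservative and weak (one-way: about 20% to 12% power against 71% to 91%, for assumed correlations of 0.5 to 0.7 and a 0.3 SD rise) or, as a complete-case repeated-measures ANOVA with C4, restricted to non-remitters.

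A reader might go further and conclude that the BDNF hypotheses cannot be tested, or that the collections in general miss the depression visits. The article does not support this. C1 to C3 align approximately, and a mixed model using actual dates could use most of the data. The BDNF work is framed as exploring associations, and the co-primary outcomes, sample size and safety assessment are untouched. It should be changed, but it does not threaten the trial's main conclusions.

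**What to change.** 1. Replace the separate t-tests and the ANOVA with the hierarchical model of Section 2.9: patient effect, collection, arm and arm by collection, using actual sampling dates.
2. Make no stand-alone comparison of ECT with MST at C4. Report C4 descriptively, labelled as session-12 non-remitters, or use it only within the model.
3. Reconcile C5, C6 and C7 with the HAMD17 visits. Either date them to those visits or keep the dates and state which HAMD17 assessment each is paired with. Correct the claim that week 24 coincides with the 3-month visit. Define C7 or delete it.

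The cost is a few sentences in the SAP and the sampling schedule and, if the first option in step 3 is taken, re-dated draws. The choice of dates is the sponsor's: keeping week 12 for C5 is acceptable if the pairing is stated. The dates should be settled before further post-treatment samples are taken.

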### 2.10. Sample Size Calculation

The software programs G * Power 3 [67] from Universität Düsseldorf, Germany, and Stata (Statacorp, College Station, TX, USA) were used to conduct calculations. The sample size was determined using parameters of α = 0.025 (one-tailed), β = 0.2, and a standard deviation of 9.5. The margin of non-inferiority (NI) was determined based on a combination of statistical reasoning and clinical judgment [68]. The lower bound of the confidence interval from a meta-analysis comparing ECT vs. sham was used to establish the NI [69]. Using a meta-analysis by the UK ECT Review Group [16], the difference in HAMD17 scores between ECT and placebo was 9.7 points (95% CI 5.7 to 13.5), with an NI value of 5.7. Despite the large margin, this NI value was deemed acceptable due to the cognitive effects of bitemporal ECT (the control comparison). Thus, MST would be a reasonable non-inferior intervention, as cognitive superiority would also need to be demonstrated. The sample size required was 88 patients, with an additional enrollment of 10% (total of 100 patients, 50 per arm) to account for attrition. For the superiority analysis, we used data from an unpublished clinical trial of 75 patients that compared the efficacy and cognitive outcomes of MST vs. ECT (personal communication from [name]). The effect size of AMT [32] after 12 treatment sessions was approximately 1.31, requiring a sample size of 26 patients to demonstrate a difference. Thus, the larger sample size from the clinical outcome study was used for the NI calculation.

## 3. Discussion

ECT is an effective alternative for treating TRD, albeit with limitations attributed to cognitive side effects [18]. Recent advancements in therapeutic modalities have introduced alternative agents and neuromodulation techniques, such as MST. By utilizing a magnetic field, MST offers a potential solution to the cognitive side effects associated with ECT by inducing seizures without directly stimulating deeper brain structures [70]. The objective of this study is to present a double-blinded, randomized, non-inferiority trial that compares the efficacy, tolerability, cognitive adverse effects, and neurophysiological biomarkers of MST to BT ECT in patients diagnosed with treatment-resistant unipolar or bipolar depression.

The primary outcome measure will be the reduction in depressive symptoms, assessed using the HAMD scale. Secondary outcome measures will include response rates, remission rates, and cognitive functioning assessed through comprehensive neuropsychological testing. Simultaneously, the evaluated biomarkers include multimodal MRI and serum BDNF levels. Evaluation of outcomes will be conducted at baseline, during the active treatment phase, and throughout a 6-month follow-up period.

Building upon previous research, the proposed protocol explores the potential of utilizing MST as an alternative form of convulsive therapy for TDR. This represents a significant advancement in the field.

The initial experiments with MST demonstrated its feasibility, tolerability, and effectiveness in both non-human primates and humans [71,72]. Shortly after, a double-blind randomized trial comparing the side effects of ECT and MST in patients diagnosed with major depression reported fewer subjective side effects and lower rates of disorientation, inattention, retrograde amnesia, and impairment of verbal fluency in the immediate post-ictal period for patients undergoing MST [70]. Since then, several studies have investigated the efficacy of MST for the treatment of depression, particularly when compared to ECT [73,74,75,76]. In general, recent studies provide support for the hypothesis that MST, when compared to ECT, exhibits non-inferiority in terms of antidepressant effects [77,78,79] and demonstrates a more favorable cognitive profile [73,74,75,77,80,81]. 

Despite the promising evidence, it is important to note that the evidence in favor of or against MST is not sufficiently robust, and further scientific evidence is required to establish its therapeutic potential. A meta-analysis conducted by Chen et al. [11] highlighted the scarcity of studies and the heterogeneity in methodologies employed, indicating the need for more research with larger sample sizes and standardized protocols. Moreover, they also emphasized that the majority of previous studies (1) primarily focused on memory when assessing cognition, neglecting other cognitive abilities; (2) lacked follow-up evaluations, thus obscuring the long-term clinical effects; and (3) predominantly utilized RUL ECT, which may be associated with lower efficacy compared to BT ECT [16], potentially overestimating the comparative antidepressant therapeutic effect of MST.

Through the implementation of a rigorous methodology to ensure validity and reliability, our study aims to address existing gaps in the literature. By extending the follow-up period beyond the active phase of the study, we seek to gain insights into the sustained benefits and relapse rates associated with MST. Furthermore, we intend to assess the effects of MST on various cognitive dimensions beyond memory assessment, providing a comprehensive understanding of its cognitive impact. Additionally, we plan to compare MST with BT ECT, taking into consideration the more favorable antidepressant efficacy profile of BT ECT. This comparative analysis will contribute to a comprehensive understanding of the therapeutic potential and effectiveness of MST in real-world clinical settings.

We anticipate that our study will provide evidence supporting the non-inferiority of MST compared to BT ECT in reducing depressive symptoms among patients with TRD. Moreover, we hope to demonstrate that MST exhibits a more favorable cognitive profile, particularly with respect to memory function, when compared to BT ECT. The availability of a viable and effective alternative convulsive therapy may improve access to treatment for drug-resistant patients who currently face severe and debilitating symptoms due to concerns or apprehensions about ECT-induced side effects.

The second significant potential of the proposed protocol, building upon prior research, pertains to the exploration of the neurobiological underpinnings of convulsive therapy. While MST theoretically provides greater control over the induction and spread of seizures, individualized treatments require knowledge of the specific biological targets to stimulate. However, the neurobiological basis of convulsive therapy and the relationship between its antidepressant and cognitive effects are not fully understood. Existing evidence primarily comes from studies on ECT, which have limitations such as small sample sizes, methodological diversity, and inconclusive results [82,83].

To the best of our knowledge, there have been fewer than five studies to date investigating the neurobiological underpinnings of MST. For example, Cycowicz et al. [84] conducted a study with rhesus macaque monkeys, randomizing them to receive ECS (form of ECT applied to animals in research studies), MST, or simulated ECT over a period of six weeks. EEG analysis revealed that MST induced lower ictal EEG power compared to ECS, primarily due to increased activation in the alpha, beta, and theta bands. Delta activity did not show significant differences between the techniques. These findings suggest that superficial cortical regions may be anatomically associated with the antidepressant effects of convulsive therapies. Additionally, the intensity of ECS stimulation influenced the expression of higher frequency bands but not delta activity. It is known that increasing the intensity of ECT above the seizure threshold leads to cognitive side effects without enhancing efficacy. This suggests that the side effects of convulsive therapy may be partially related to the stimulation of deeper brain regions. 

One of the challenges in investigating the neurobiological basis of convulsive therapy pertains to the fact that these techniques exhibit therapeutic effects on various pathologies that are conceptually distinct. Their mechanism of action involves different levels of the biological cascade, including cell receptors, gene expression, protein synthesis, neuroplasticity, and connectivity between different brain circuits. Consequently, some of the biomarkers considered crucial may only be epiphenomena in relation to the antidepressant response. In this sense, the main question to be addressed is the extent of neuroanatomical overlap between the clinical effects of both modalities of convulsive treatment. This is one of the innovations of our protocol, which provides an opportunity to advance our understanding of the mechanisms of action of convulsive therapy in the treatment of disorders such as depression.

Another significant innovation of our protocol is the combination of different biomarkers, including multimodal neuroimaging. MRI images can be used to measure phenotypic variations in specific brain circuits that represent a unique interaction between genes and the environment and are associated with specific behavioral changes [85]. Most studies that have analyzed these biomarkers in ECT studies have only utilized a single MRI modality [86]. The use of a combination of different MRI parameters, sensitive to complementary tissue characteristics, can provide a basis for the construction of more precise endophenotypes, facilitating the identification of patient groups more likely to respond to specific interventions [87], contributing to the development of precision psychiatric clinical practice.

Comprehending the neurobiological foundations of convulsive therapy holds the potential to enable precise targeting of circuits implicated in specific symptoms while preserving cognitive functions, thereby reducing stigma and enhancing treatment accessibility. Furthermore, this knowledge can provide guidance for future research endeavors and drive advancements in the development of current therapeutic devices. Moreover, unraveling these biomarkers can contribute to our understanding of the intricate pathophysiology of depression and shed light on the neural mechanisms underlying the antidepressant effects of alternative treatment modalities, including pharmacotherapy.

Despite the clinical significance and robustness of this protocol, it is crucial to address several limitations. Firstly, the absence of a placebo control group hinders the ability to differentiate the specific effects of the interventions from placebo effects. A placebo control group would provide valuable insights and enhance the internal validity of the study. Secondly, the recruitment being limited to a single institution in Brazil raises concerns about the generalizability of the findings. It is important to recognize that the utilization of ECT in Brazil is typically limited to severe cases due to resource constraints, potentially limiting the applicability of the results to broader populations. Furthermore, the lack of assessment of serum drug levels represents a limitation in confirming the presence of pharmacological resistance in the study participants.

Additionally, the relatively short duration of follow-up restricts the ability to comprehensively evaluate the sustained effects of the interventions. A longer-term assessment would offer a more complete understanding of the long-lasting impacts. Moreover, the reliance on self-reported measures introduces the potential for recall bias and social desirability bias, which may affect the accuracy of the collected data. It is crucial to consider these limitations and interpret the findings in light of these potential biases. Lastly, the study population consists of a specific demographic group, and caution should be exercised when extrapolating the results to other populations with different characteristics, highlighting the need for further research in diverse populations to ensure broader applicability.

On the other hand, our protocol exhibits several strengths that enhance its scientific value. Firstly, it introduces a novel treatment option, MST, which has demonstrated promising safety and efficacy in preliminary evidence. Secondly, the protocol adopts a double-blinded, randomized, non-inferiority study design, ensuring a rigorous approach to comparing the efficacy and safety of MST and ECT. This design enhances the internal validity of the study. Thirdly, the protocol encompasses a comprehensive set of outcome measures, including assessment of depressive symptoms, cognitive performance, neurophysiological biomarkers, and neurotrophic markers. This multidimensional assessment provides a more comprehensive understanding of the effects of the interventions. Fourthly, the protocol incorporates multimodal nuclear magnetic resonance imaging (MRI) and analysis of serum neurotrophic markers to investigate the neurobiological basis of seizure therapy. This neurobiological investigation contributes to a deeper understanding of the underlying mechanisms of treatment-resistant depression (TRD) and the effects of the interventions. Fifthly, the evaluation of neurophysiological biomarkers as secondary outcomes has the potential to predict the antidepressant and cognitive effects of both techniques, paving the way for the development of individualized treatment approaches in the future. Sixthly, the protocol includes intensive clinical and neurocognitive assessments before, during, and after treatment, ensuring close monitoring of patient progress and ensuring their safety throughout the study. Lastly, the protocol incorporates longitudinal follow-up assessments post-treatment to monitor the long-term outcomes of patients, providing valuable insights into the durability of treatment effects. Collectively, these strengths contribute to the scientific robustness of our protocol and enhance its potential to generate valuable insights into the effectiveness and mechanisms of action of MST and ECT in the treatment of TRD.

In general, our results can contribute to the development of new strategies for the treatment of depression. However, it is important to note that the translation of research protocols to clinical practice requires further validation, replication, and consideration of real-world challenges and constraints. The results of this study would be an important step towards establishing MST as a safe and effective treatment option for TRD, but additional research and practical implementation considerations are necessary before widespread adoption in clinical settings.

